0.05. Although the precise statistical power of the study will depend on the
bandwidth, the Clinical Practice Research Datalink database will provide more
than the required number of patients (Table 1) [37].

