## Statistical methods

Our initial analysis (Table 1) suggests that
the proportion of patients receiving a named accountable general practitioner is
discontinuous at the threshold, but this will be confirmed on receipt of the data.
We will also confirm that, although we would expect a trend in certain covariates
across age, there are no discontinuities in these covariates at age 75. This
comparison will be done graphically and include all patients, regardless of actual
treatment assignment. We do not expect such discontinuities to occur, but if they do
exist, this would lead us to question the validity of our study design.

As mentioned previously, the proportion of patients receiving a named accountable
general practitioner is unlikely to jump from 0 to 100% at age 75. It will therefore
be appropriate to apply a fuzzy regression discontinuity design [31], by fitting four regression models. Two
models will relate the outcome to a polynomial function of age: one model will be
fitted for people whose age lies within the bandwidth below the threshold and the
other model for people within the bandwidth above the threshold. The final two
models have treatment assignment as their dependent variable rather than outcome.
All models will use ordinary least squares regression and include patients
irrespective of their actual treatment assignment. We will calculate the estimated
treatment effect as the difference between the predictions of the two outcome models
at age 75, divided by the difference between the predictions of the two treatment
models at age 75.

The analysis will have regard to the rounded nature of the running variable (i.e.
age), resulting from the use of year of birth rather than full date of birth. This
will exclude the use of very small bandwidths, and so we will use a larger interval
spanning several years and model any trend in the endpoints by age using parametric
approaches based on polynomial functions [42,43]. In the absence of
information on full date of birth, it will not be possible to establish for a given
patient born in 1939 what date they turned 75, and therefore which side of the
threshold the patient is at the index date. We will remove the risk of
misclassification by excluding all patients born in 1939 when fitting the regression
models and making a small extrapolation around age 75 [42]. A final consideration is that, when the running variable
is only observed at discrete points, discretisation bias can occur because a change

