### Required sample size

We believe that a 5% change in the number of general practice contacts would
represent a meaningful difference to general practice workload, since this
represents approximately one extra appointment per working day for an average
general practitioner [46]. Assuming an
average of 5 general practitioner contacts per 6-month period in the absence of
a named accountable general practitioner [47], and a standard deviation of 6 contacts [47,48], we will need
24,212 patients in each treatment group, at 90% power and two-sided p-value of

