### Strengths and limitations

Four characteristics of this study distinguish it from existing work in this
area. First, this study will examine a national policy intervention to integrate
care, as opposed to particular local initiatives to encourage more integrated
services. The nature of national initiatives means that the prescribed
intervention might not suit all local contexts and there may be limited local
buy-in to change, potentially limiting effectiveness. However, contracts are a
potentially important method of encouraging more continuity of care, and we are
not aware of previous studies that have investigated the effectiveness of such
an approach.

Second, previous studies have examined integrated care within pilot areas [21], but the current study will use a large
database to examine a national sample of general practices, increasing the
generalisability of its results. The Clinical Practice Research Datalink
database is broadly representative of the UK population [41], though our sample will be limited to those that have
consented to participate in the Clinical Practice Research Datalink linkage
scheme and in addition have submitted data to Clinical Practice Research
Datalink in a timely fashion. While it will not be possible for us to document
the intervention as closely as pilot studies, we will investigate whether the
effectiveness of the policy varies according to local characteristics. If some
areas perform better than others, then future studies could use qualitative
methods to construct theories for why these areas saw more promising results
[50]. The current study is an example
of a relatively new approach that applies surveillance methods to national
databases to identify areas of good practice, rather than starting with
prospective studies of a small number of selected pilots, which may not show the
anticipated returns [51].

Third, the large sample size means that we will have statistical power to detect
small effects, such as a 5% change in the number of general practitioner
contacts. This is important because many previous studies of out-of-hospital
interventions have assumed relatively large effect sizes when estimating the
required sample size, for example that emergency hospital admissions could be
reduced by 15% within 12 months [52,53]. Where such studies fail to detect
changes, it is unclear whether this is due to an ineffective intervention or
simply that the study was underpowered to detect small yet meaningful effects.

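### Having more than 24,212 patients per group does not show 90% power for the planned fuzzy regression discontinuity estimator

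*Protocol article*

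**What the plan says.** The Required sample size section takes a 5% change as the target ("We believe that a 5% change in the number of general practice contacts would" matter for workload). It assumes an "average of 5 general practitioner contacts per 6-month period in the absence of" a named practitioner and "a standard deviation of 6 contacts", and arrives at "24,212 patients in each treatment group, at 90% power and two-sided p-value of" 0.05. It accepts that exact power varies with the bandwidth, but still concludes that the database supplies more "than the required number of patients (Table 1) [37". The Strengths and limitations section then lists power as an advantage: "Third, the large sample size means that we will have statistical power to detect" small effects, with 5% as its example.

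The Statistical methods section plans a different kind of estimate. Separate polynomials in age are fitted by least squares on each side of 75. The authors avoid "misclassification by excluding all patients born in 1939 when fitting the regression" models, and extrapolate to 75. They define the "treatment effect as the difference between the predictions of the two outcome models" at 75, divided by the corresponding difference in treatment receipt. Bandwidth is left to cross-validation, and the polynomial order is not stated.

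**The concern.** The sample size inputs are a difference, a standard deviation, a power and a significance level. Those are the inputs for comparing two means. Nothing is shown for the treatment jump, for prediction at the edge of a fitted trend, or for the dropped birth year, and all three inflate the variance of the planned estimate. If the requirement was derived for a simpler comparison, meeting it says little about power for the analysis that will be run.

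At stake is how a null result is read. The Strengths and limitations section criticises earlier studies because their null findings could not be told apart from low power. If this study has good power only under some permitted specifications, a null result could be over-read as excluding a 5% effect.

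**Working it through.** **Inputs.** From Required sample size: difference 0.05 × 5 = 0.25 contacts, SD 6, two-sided 0.05, 90% power. From Table 1: receipt 67,770/84,931 = 0.798 at ages 75-79 and 5,420/105,250 = 0.051 at ages 70-74, a jump of 0.746. Counts per year of age: 105,250/5 = 21,050 below and 84,931/5 = 16,986 above. From Study cohorts: ages 65 to 85, so at most 10 single-year ages on each side once 1939 births are dropped.

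**Step 1: the plan's own figure.** n per group = 2 × 6² × (1.960 + 1.282)² / 0.25² ≈ 12,105, or 24,210 in total. The stated 24,212 matches the two-group total. Read literally as a per-group number, it gives 99.6% power for a comparison of two means, not 90%.

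**Step 2: the treatment jump alone.** If the 5% is the effect in compliers, the outcome jump to detect is 0.25 × 0.746 = 0.187, and required n rises by 1/0.746² = 1.79, to about 21,700 per group. At 24,212 per group, power is still about 93%.

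**Step 3: extrapolation.** With equal numbers at ages 1 to h years from 75, the variance of a linear prediction at 75 is inflated by V = 1 + 3(h+1)/(h−1). This gives 7.0 for h = 3, 5.5 for h = 5, 5.0 for h = 7 and 4.67 for h = 10. For a quadratic, V is the intercept element of the inverse moment matrix: 57 for h = 3, 23 for h = 5 and 13.8 for h = 10.

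**Step 4: power at 24,212 per side.** The standard error of the outcome jump is 6 × √(2V/24,212). For linear, h = 5, this is 0.128. Power is Φ(0.187/0.128 − 1.96) = 31%. Over h = 3 to 10 the range is 25-35% for linear and 7-15% for quadratic fits. The number needed per side for 90% power is 12,105 × 1.79 × V: about 119,500 (linear, h = 5), 101,400 (linear, h = 10), 499,700 (quadratic, h = 5) and 300,500 (quadratic, h = 10).

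**Step 5: power at the patients available.** Assume Table 1's counts per year of age hold across the window. The standard error is 6 × √(V/(21,050h) + V/(16,986h)). For linear, h = 5, it is 0.0649, and power is Φ(0.187/0.0649 − 1.96) = 82%. The minimum detectable effect (MDE) at 90% power is 3.242 × SE / 0.746, as a percentage of 5 contacts.

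| Fit, years each side | Power, 5% as complier effect | Power, 5% as overall jump | MDE, complier effect |
|---|---|---|---|
| Linear, 5 | 82% | 97% | 5.6% |
| Linear, 7 | 95% | >99% | 4.5% |
| Linear, 10 | 99% | >99% | 3.7% |
| Quadratic, 5 | 29% | 47% | 11.5% |
| Quadratic, 10 | 73% | 93% | 6.3% |

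Table 1's older group includes the 1939 births that will be dropped. Using only the ages it covers, 70-74 against 76-79 (84,931 × 4/5 = 67,945 above), linear power is 75% and quadratic power 22% on the complier reading.

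These figures ignore sampling error in the treatment jump, practice clustering and the exclusions that Table 1's note says were not all applied.

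**The case against.** Five points can be made for the plan.

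- **The database is much larger than 24,212 per side.** This stands. A reader might infer from the 31% in step 4 that the study has 31% power. The documents do not support that: it is one specification at a sample size the study will not use. The methods rule out very small bandwidths, and a linear fit over 7 or 10 years each side exceeds 90% on the assumptions above.
- **Both inflations may not have been ignored.** A reader might infer that the fuzzy scaling was overlooked. That cannot be established: a factor of 2 would cover the 1.79 in step 2, and the article does not say where 24,212 comes from. But a factor of 2 falls well short of the combined 8.4 (linear, 10 years) to 9.9 (linear, 5 years).
- **The text is hedged.** The 90% appears only with the sample size. The next sentence says power depends on bandwidth, and Strengths and limitations gives no percentage. This stands in part, but the hedge omits polynomial order, which matters more than bandwidth in the table, and the requirement is still declared met.
- **The 5% may be the overall change at the threshold**, since it is justified by workload. The article does not settle this. On that reading the table's third column applies, yet power at 24,212 per side is still at most 56%.
- **Bandwidth, order and power tables can sit in a fuller plan.** This is fair, and their absence here is not the point. The point is that a stated number and the conclusion drawn from it do not fit the stated estimator.

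**Conclusion.** The point holds in this form: exceeding 24,212 per group does not establish 90% power for the planned estimator. The number is not reproduced as a per-group requirement from its own inputs, which give about 12,105. Under every linear or quadratic fit checked over 3 to 10 years, 24,212 per side falls far short of 90%. Most of the loss comes from extrapolating to 75, not from the fuzzy scaling.

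Whether the study itself has adequate power depends on choices still open. On the complier reading it ranges from about 29% (quadratic, 5 years) to 99% (linear, 10 years). This rests on constant counts per year of age, which is favourable at the oldest ages. With 120,000 to 140,000 patients above the threshold over 10 years, instead of about 170,000, linear power stays at 98-99% and quadratic power is 64-68%. Further exclusions and practice clustering would be expected to lower all these figures.

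**What to change.** Rewrite the Required sample size paragraph:

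1. Correct 24,212 to a total, or state the inflation factor it contains and why.
2. Compute power from the variance of the planned estimator: 36 × (V_below/n_below + V_above/n_above), divided by the squared treatment jump, with 1939 births left out.
3. State whether the 5% is an effect in compliers or the overall change at the threshold.
4. Report the minimum detectable effect at 90% power by bandwidth and polynomial order, as in the table above, updated to the final cohort.
5. Qualify the conclusion that the database is large enough, and the power claim in Strengths and limitations, by naming the specifications to which they apply.

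The data, endpoint and estimator do not change, and no extra patients are needed. The cost is a rewritten paragraph and a less favourable figure for some specifications.

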## Discussion

### Contribution of the study

Both policy-makers and patients believe that general practitioners are best
placed to coordinate their care [13,24,49], but many patients cannot see their preferred doctor [9]. The current study will evaluate the
introduction of a named accountable general practitioner for each patient aged
75 or older and the requirement to communicate to patients their specific
responsibilities for coordinating health and social care. As well as assessing
impacts on various metrics relating to continuity of care, including the Usual
Provider of Care index, we will investigate the variability in the effectiveness
of the policy between general practices with different characteristics.

### Strengths and limitations

Four characteristics of this study distinguish it from existing work in this
area. First, this study will examine a national policy intervention to integrate
care, as opposed to particular local initiatives to encourage more integrated
services. The nature of national initiatives means that the prescribed
intervention might not suit all local contexts and there may be limited local
buy-in to change, potentially limiting effectiveness. However, contracts are a
potentially important method of encouraging more continuity of care, and we are
not aware of previous studies that have investigated the effectiveness of such
an approach.

Second, previous studies have examined integrated care within pilot areas [21], but the current study will use a large
database to examine a national sample of general practices, increasing the
generalisability of its results. The Clinical Practice Research Datalink
database is broadly representative of the UK population [41], though our sample will be limited to those that have
consented to participate in the Clinical Practice Research Datalink linkage
scheme and in addition have submitted data to Clinical Practice Research
Datalink in a timely fashion. While it will not be possible for us to document
the intervention as closely as pilot studies, we will investigate whether the
effectiveness of the policy varies according to local characteristics. If some
areas perform better than others, then future studies could use qualitative
methods to construct theories for why these areas saw more promising results
[50]. The current study is an example
of a relatively new approach that applies surveillance methods to national
databases to identify areas of good practice, rather than starting with
prospective studies of a small number of selected pilots, which may not show the
anticipated returns [51].

Third, the large sample size means that we will have statistical power to detect
small effects, such as a 5% change in the number of general practitioner
contacts. This is important because many previous studies of out-of-hospital
interventions have assumed relatively large effect sizes when estimating the
required sample size, for example that emergency hospital admissions could be
reduced by 15% within 12 months [52,53]. Where such studies fail to detect
changes, it is unclear whether this is due to an ineffective intervention or
simply that the study was underpowered to detect small yet meaningful effects.
Moreover, where interventions are implemented haphazardly or with limited
fidelity to the intervention design, this might reduce the power of the study,
underscoring the need to assume conservative effect sizes when estimating the
required sample size.

Finally, many previous studies of integrated care interventions have used study
designs that are susceptible to con-founding arising from differences in
unobserved or observed patient characteristics [21,28]. In the current study,
the use of a regression discontinuity design will largely avoid these
concerns.

One limitation of this study is that the lack of full information on date of
birth means that our estimates are dependent on model specification [33], though we will test the sensitivity of
our findings. Also, the estimated treatment effects will only apply to
individuals aged close to 75 years, while younger or older groups might see
larger or smaller treatment effects. Our findings will also apply to the subset
of patients who are compliers and are not in the top 2% risk category. By
excluding the 2% of the population most at risk, we are omitting some of the
patients most in need of integrated care. However, a more intensive intervention
is currently being targeted at this group [54], and this intervention needs to be evaluated as a separate
study, something we might do at a later stage.

This study will examine four endpoints that could plausibly be affected by named
accountable general practitioners, namely general practitioner contact rates,
longitudinal continuity of care, referrals to specialist care and numbers of
diagnostic tests. It is possible that improvements in these endpoints may take
longer than 6 months to materialise but, to the extent that this is due to poor
implementation, the subgroup analysis may be informative. Moreover, while the
study will examine longitudinal continuity of care, it will not examine other
aspects of continuity, such as informational or management continuity [12,13], nor the patient experience of care.

We cannot determine whether the particular general practitioner contacts,
diagnostic tests and referrals to specialist care were appropriate. Although
continuity of care indices have been successfully applied to Clinical Practice
Research Datalink data in the past [20],
difficulties in analysing longitudinal data have been highlighted [12]. For example, although a staff
identifier is entered onto the computer system, practices may use shared login
details, particularly for locum doctors, which would affect the Usual Provider
of Care index.

We will not examine impacts on hospital admissions or disease control beyond the
frequency of diagnostic tests, as these are unlikely to be affected by the
policy within 6 months. Our endpoints are likely to be on the causal pathway for
better disease control and reduced admissions, and so our findings will indicate
whether investigation of additional metrics is warranted. The limitations of the
data mean that it is not possible to examine impacts on social care utilisation
or access to primary care.

## Conclusions

This study will analyse a national policy initiative aimed at promoting integrated
care through increasing the continuity of care and prompting communication about
accountability for care coordination with patients. It will use surveillance of
national data to identify sites demonstrating promising outcomes associated with a
particular integrated care initiative. This study could complement existing
approaches aimed at in-depth examination of particular pilot sites, while removing
the threats to confounding from treatment selection associated with many cohort
studies.

### Research governance

The Independent Scientific Advisory Committee for MHRA Database Research has
approved this study (reference: 15_070R). Ethical review was not required as
this is a retrospective study of pseudonymised, routinely collected data.
